## Abstract

**Background:**

*Xingnaojing* injection (XNJ) is widely used for the treatment of stroke in China. However, there is currently a lack of high-quality evidence of its efficacy for acute ischemic stroke. The main objective of this study is to determine whether the addition of XNJ to standard care improves the 3-month functional outcome in patients with acute ischemic stroke (AIS).

**Methods/design:**

The XMAS study is a multicenter, prospective, randomized controlled, open-label trial with a blinded endpoints design. A total of 720 patients will be randomly allocated to either the intervention or the control group in a 1:1 ratio. The intervention group receives XNJ combined with standard care, and the control group receives standard care alone. XNJ will be administered intravenously every 12 h for 10 days. The primary outcome is the proportion of patients who are independent at 3 months after stroke onset defined as a modified Rankin Scale score of 0 to 2. Secondary outcomes include early neurological deterioration at 48 h, the change in National Institutes of Health Stroke Scale score, patient-reported outcome, symptomatic intracranial hemorrhage at 10 days, the Barthel Index score, deaths from any cause and cardiovascular events at 3 months.

**Discussion:**

The results of this trial will provide critical evidence for XNJ in the treatment of AIS as a complementary approach that can be initiated after reperfusion therapy or when the AIS is not eligible for thrombolytic treatment.

**Trial registration:**

Clinical Trials.gov, ID: NCT02728180. Registered on 28 March 2016.

**Electronic supplementary material:**

The online version of this article (doi:10.1186/s13063-017-2222-y) contains supplementary material, which is available to authorized users.

## Background

Globally, stroke is one of the leading causes of death and long-term disability [1]. In the past two decades, the burden of stroke has increased significantly in terms of the absolute number of people with incident stroke, number of deaths, and disability-adjusted life years (DALYs) lost especially in developing countries [2]. According to a nationwide population-based survey in China, there are approximately 2.4 million new strokes and 1.1 million stroke-related deaths annually, with 11.1 million stroke survivors, which consequently results in a huge financial burden [3].

Despite recombinant tissue plasminogen activator (rt-PA) and emerging evidence for endovascular treatment [4], only a few highly selected patients with acute ischemic stroke (AIS) receive thrombolytic therapy due to strict selection criteria. From the Chinese National Stroke Registry, 21.5% of patients with acute stroke presented to the emergency department (ED) within 3 hours, 12.6% were eligible for thrombolytic treatment, and only 1.6% received intravenously administered rt-PA therapy [5]. The lack of effective and widely applicable therapeutic approaches for AIS has resulted in a growing interest in traditional Chinese medicine (TCM).

*Xingnaojing* injection (XNJ) was extracted by modern biotechnology from a well-known Chinese patent medicine named *An-Gong-Niu-Huang Wan* which was first documented in *Wen Bing Tiao Bian*, a classical work of TCM published in 1798. XNJ has been approved by the China Food and Drug Administration (CFDA) and is widely used for the treatment of stroke [6]. XNJ consists of four Chinese herbs: *Moschus*, *Radix curcumae*, *borneol*, and *Fructus gardeniae*. Previous studies have demonstrated that XNJ may has multiple neuroprotective mechanisms in terms of inhibiting glutamate-induced apoptosis [7], anti-autophagy via the p53-DRAM signaling pathway [8], decreasing gamma-aminobutyric acid (GABA) [9], improving neurobehavioral disturbances, as well as reducing infarct size [10]. Recently, a systematic review and meta-analysis to assess the efficacy of XNJ for stroke demonstrated that XNJ may reduce brain injury and improve functional recovery after stroke. Due to methodological limitations of the included trials, however, the efficacy of XNJ for ischemic stroke is still not established [11].

Thus, in the present study, we aim to determine whether the addition of XNJ to standard care, intravenously administered within 24 h of symptom onset, improves the 3-month functional outcome in participants with AIS.

## Methods/design

### Study design

The *Xingnaojing* for Moderate-to-severe Acute ischemic Stroke (XMAS) trial is a multicenter, prospective, randomized controlled, open-label trial with blinded endpoints assessment (PROBE design). We compare XNJ, in combination with guideline-based standard care, versus standard care alone in patients with acute ischemic stroke within 24 h after stroke onset. A completed Standard Protocol items: Recommendations for Interventional Trials (SPIRIT) Checklist for the trial is available in Additional file 1.

### Recruitment

Patients will be recruited from 30 tertiary public hospitals throughout China with EDs and neurology wards that receive patients with AIS. The recruitment started in March 2016 and is estimated to end in January 2018. Patients with moderate-to-severe AIS within 24 h after stroke onset will be screened for eligibility according to the inclusion and exclusion criteria. Moderate-to-severe was defined as the National Institutes of Health Stroke Scale (NIHSS) scores ranging from 5 to 20. Time of stroke onset is defined as the last time when the patient was witnessed to be well. Those who have stroke symptoms upon awakening (wake-up stroke) will be considered to have their onset at beginning of sleep. Only those who meet the inclusion criteria and willingly provide written informed consent will be included. The flow diagram of this study is shown in Fig. 1.

**Fig. 1 Fig1:**
[figure not shown]
Flow diagram of the *Xingnaojing* for Moderate-to-severe Acute ischemic Stroke (XMAS) study

### Inclusion criteria

Acute ischemic stroke within 24 h of symptom onsetNIHSS score ≥ 5 and ≤ 20Age ≥ 35 and ≤ 80 yearsPatient or legally authorized representative has signed informed consent

### Exclusion criteria

Planned or already receiving endovascular treatmentSuspected secondary stroke caused by tumor, brain trauma, or hematological diseasesAlready dependent in activities of daily living before the present acute stroke (defined as modified Rankin Scale score ≥ 2)Other conditions that lead to motor dysfunction (e.g., severe osteoarthrosis, rheumatoid arthritis)Significant renal or hepatic insufficiency (defined as a serum creatinine concentration, alanine aminotransferase (ALT), or aspartate aminotransferase (AST) value that is twice the upper limit of normal)Life expectancy of 3 months or less due to other life-threatening illness (e.g., advanced cancer)Other conditions that render outcomes or follow-up unlikely to be assessedKnown to be pregnant or breastfeedingCurrently receiving an investigational drug

### Randomization

All participants will be randomly allocated to the intervention group or the control group in a 1:1 ratio. The randomization procedure will be computer- and web-based, using permuted blocks, and will be stratified for medical center. The randomization algorithm for the study will be generated and uploaded to the randomization system before recruitment. It will not be possible to know the treatment allocation before randomization. The password-protected randomization system requests a few key items of baseline data including the time of stroke onset, NIHSS score, date of birth, as well as a double check on inclusion and exclusion criteria, which are then entered with the computer keypad or tablet computer. When the data have been entered and checked, the computer will generate the treatment allocation. Participants who do not meet the criteria will be excluded by the system automatically and will not be randomized.

### Blinding

In this PROBE design trial, both participants and treating clinicians will be aware of the treatment assignment. Information including NIHSS score, Glasgow Coma Scale (GCS) score, and Patient-reported Outcome (PRO) score will be assessed by independent assessors who are blind to the assignment and treatment. Patients will be contacted over the telephone by independent trained interviewers, who will use standard structured scripts to collect planed data at 30 days and 3 months after stroke onset. The principal investigator, statistician, and outcomes assessors were unaware of the treatment assignments throughout the trial until the database was locked.

### Interventions

Patients randomly assigned to the intervention group will receive XNJ injection, which will be manufactured by the Jiminkexin Group, combined with standard stroke care. XNJ will be administered intravenously in the ED or neurology ward immediately after completion of the randomization. The infusion will contain 20 ml XNJ diluted in 250 ml normal saline, infused every 12 h for 10 days. All information regarding XNJ administered to each participant will be recorded by nurses including dosage, administration time, and details of discontinued treatment.

Those who are assigned to the control group will be given standard stroke care alone. The standard stroke care follows the current national guidelines for acute ischemic stroke from the Chinese Society of Neurology, including anti-platelet therapy, control of vascular risk factors, and appropriate rehabilitation, which will be determined by the attending physician. Treatment with tissue plasminogen activator (rt-PA) within 3 to 4.5 h of symptom onset, after exclusion of intracranial hemorrhage, is encouraged in participants who meet thrombolytic treatment criteria outlined in guidelines.

Neither traditional Chinese herbal medication nor acupuncture is allowed during the hospitalization. All concomitant medications will be recorded in the Case Report Forms (CRFs) including the name, dosage, and course of these medications.

Participants may withdraw at any time during the trial. Investigators will discontinue the treatment in the following cases: the occurrence of serious adverse events; at the request of participant or legally authorized representative to discontinue; and other reasons for consideration of safety. All reasons of discontinuing will be recorded in the CRFs.

### Outcome measures

#### Primary outcome

The primary outcome is the proportion of patients independent at 3 months after stroke onset defined by a mRS score of 0, 1, or 2. Scores on this scale range from 0 to 6, with higher scores indicating greater disability [12].

### Secondary outcomes

Comparison of the change of degree of neurological deficit from baseline to day 10 or discharge, according to the NIHSS scores ranging from 0 to 42, with higher scores indicating more severe neurological deficits [13]Comparison of the PRO scale of stroke at 10 days, which consists of four dimensions including the influence on physical, emotional, and social functioning, as well as the overall satisfaction with treatment [14]The proportion of patients with a Barthel Index (BI) score of ≥ 90 at 30 days and 3 months after stroke onset. The BI is used to evaluate the activities of daily living, ranging from 0 to 100, with higher scores indicating more independence [15]The proportion of early neurological deterioration (END), defined as an increase of 3 points or more in the NIHSS score between baseline and 48 hThe proportion of symptomatic intracranial hemorrhage (sICH) occurrence within 10 days of stroke onset, defined as any ICH related to a decline in neurological status or the development of new neurological symptoms in the judgment of the clinical investigatorThe incidence of cardiovascular events, which consist of recurrence of stroke or myocardial infarctionThe incidence of deaths from any cause within 10 days and 3 months after symptom onsetSafety endpoints, which consist of any adverse events, results of electrocardiography, vital signs and laboratory tests (complete blood count, chemistry, and urinalysis)

### Safety reporting

Adverse events (AEs) are defined as any unfavorable and unintended sign, symptom or disease arising in participants in both groups during the trial period, whether or not related to the experimental treatment. The investigator should take appropriate measures to ensure the safety of the participants and follow up the outcome of any AEs (clinical signs, laboratory values or other, etc.) until the return to normal or stabilization of the patient’s condition. All AEs reported by the subjects, caregivers, or observed by the treating physicians during this trial will be recorded, including the nature of each event, onset date and time, duration, intensity, assessment of its cause, specific therapy and its outcome.

A serious adverse event (SAE) is one that can fatal or life-threatening, requires prolonged hospitalization, or results in permanent or substantial disability. In case of SAEs, the principal investigator will be notified by email or telephone within 24 h. The principal investigator subsequently reports a SAE to the Data Safety Monitoring Board (DSMB). This is an independent committee of trial experts that will focus on safety monitoring to ensure that the study meets the highest standards of ethics and patient safety.

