**Table 1 Tab1:**
[figure not shown]
Schedule of trial-related activities

Abbreviations: *CT* computed tomography scan, *MRI* magnetic resonance imaging, *ECG* electrocardiogram, *NIHSS* National Institutes of Health Stroke Scale, *GCS* Glasgow Coma Scale, *mRS* modified Rankin Scale, *PRO* Patient-reported Outcome Scale of Stroke, *TCM* traditional Chinese medicine, *sICH* symptomatic intracranial hemorrhage, *AEs* adverse events, *SAEs* serious adverse events

Baseline characteristics are collected including demographics, medical history, previous medication, pre-stroke mRS, vital signs, GCS score, NIHSS score, Diagnostic Scale of Syndrome Elements in Ischemic Stroke (DSSEIS) score, time of symptom onset, time of ED arrival, time of intervention, stroke subtypes, and complications.

Independent assessors at each center, who were trained before enrollment, will be responsible for assessment including NIHSS score, GCS score, DSSEIS score, and PRO score at 48 h, 7 days, and 10 days or at discharge if earlier.

In addition, CD-ROM copies of all computed tomography (CT) and magnetic resonance imaging (MRI) scans will be collected from participating centers and assessed blindly by independent neuro-radiologists at the central trial imaging analysis center at the Institute for Cerebrovascular Disease of Beijing University of Chinese Medicine (ICVD).

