### Follow-up

Independent interviewers will contact all subjects by telephone and collect follow-up information using standard Telephone Interview Forms (TIFs) at 30 days and 3 months after stroke onset. The TIF is a standard questionnaire including structured mRS, BI, locations, stroke recurrences, new-onset vascular events, self-reported information on medication use, and rehabilitation at follow-up period. All telephone interviewers, with a neurological background, will be trained to contact participants according to a standard operating procedure (SOP) before trial recruitment. All interviews will be recorded and retained.

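### A new hospital admission is not in itself an SAE criterion, so short readmissions after discharge may miss the 24-hour notice and the DSMB

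*Protocol article*

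**What the plan says.** The protocol article defines seriousness once, under Safety reporting: an SAE is an event that is fatal or life-threatening, or one that "requires prolonged hospitalization, or results in permanent or substantial disability". No other section adds a criterion. SAEs are to be notified to the principal investigator within 24 h and then passed to the DSMB. No such route is described for other adverse events.

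The same section sets a wide window for adverse events, namely those "arising in participants in both groups during the trial period, whether or not related to the experimental treatment". It also provides for recording the non-serious ones: "All AEs reported by the subjects, caregivers, or observed by the treating physicians during this trial will be recorded".

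In-hospital assessments under Data collection end at "10 days or at discharge if earlier". After that, according to Follow-up, interviewers "collect follow-up information using standard Telephone Interview Forms (TIFs) at 30 days and 3 months after stroke onset". The items named for that form include the mRS, the Barthel Index, locations and stroke recurrences, and then "new-onset vascular events, self-reported information on medication use, and rehabilitation at follow-up period".

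Under Interventions, the occurrence of an SAE is one of the listed reasons for stopping treatment.

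**The concern.** Every participant enters the trial through an emergency department or neurology ward. In the first days, a criterion based on a prolonged stay can work, because there is a stay to prolong. After discharge there is none, and the hospital-based sign of a serious event is then an admission. The definition does not name one.

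What is at stake is safety oversight. The 24-hour notice and the stated path to the DSMB depend on the SAE label. If some readmissions do not receive it, the board learns of them later or by a route that the article does not describe, and the reported SAE count after discharge is too low. Treating clinicians know the assignment (Blinding section) and 30 hospitals recruit (Recruitment section), so a clause that can be read in two ways also leaves room for like events to be classified differently.

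**Working it through.** The plan gives no figure on this point, so there is none to reproduce. The check sets the sections side by side.

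**Step 1: is there time at risk after discharge?** Treatment lasts 10 days (Interventions), in-hospital assessment allows for discharge before day 10 (Data collection), and follow-up ends at 3 months (Follow-up). The article does not say when participants usually go home. As an illustration, take 3 months as 90 days and assume a discharge day:

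- discharge on day 10: (90 − 10) / 90 = 80 / 90 = 89% of the period lies after discharge;
- discharge on day 30: (90 − 30) / 90 = 60 / 90 = 67%.

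Under either assumption most of the adverse-event window falls after discharge.

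**Step 2: what does the hospital clause cover?** It has two possible readings. Reading A is that the event extends a current stay. Reading B is that the event needs a lengthy stay, whether or not the patient was already in hospital.

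| Event | Reading A | Reading B | With new admission added |
|---|---|---|---|
| Fatal or life-threatening | SAE | SAE | SAE |
| Leaves permanent or substantial disability | SAE | SAE | SAE |
| In-hospital event that delays discharge, none of the above | SAE | SAE if the stay counts as lengthy | SAE |
| Long readmission, none of the above | AE only | SAE | SAE |
| Short readmission, none of the above | AE only | AE only | SAE |

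The last row is the gap that remains under both readings. The third and fourth rows show where two sites could classify the same event differently.

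**Step 3: where does an event in the last row go?** If reported, it is recorded as an adverse event, because the recording rule covers all of them. If it is a recurrent stroke or a myocardial infarction, it also counts in the secondary outcome on cardiovascular events. In neither case does the article attach the 24-hour notice or the DSMB report.

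**Step 4: can the number be estimated?** No. The article gives no readmission rate and no split of readmissions by severity or length.

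**The case against.** The strongest case on the other side has five parts.

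*The other criteria still apply.* A reader might infer that a readmission after discharge is never an SAE. The article does not support that. A readmission that is fatal, life-threatening or disabling qualifies whatever the hospital clause means, and liver injury, renal injury or infection can be any of these. Under Reading B a lengthy readmission qualifies too. This narrows the point to the last row of the table, but that row stands.

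*The events are not lost.* Reported adverse events are recorded with their intensity, cause, therapy and outcome, any adverse event is a safety endpoint, and deaths, recurrent stroke and myocardial infarction are counted separately. The article also does not say that the DSMB sees nothing except SAEs. This stands, and it confines the harm to expedited notice and SAE counts.

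*The article condenses a fuller protocol.* The sentence is roughly worded, and site instructions may list more criteria. That is possible. But the article states the criteria as a list with nothing to mark it as partial, so the point concerns a stated rule rather than an omitted detail.

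*The telephone form may already ask.* A reader might conclude from the listed items that the form has no question on admissions or other adverse events. That cannot be shown. The list is introduced as what the form includes, it names locations, and Table 1, whose abbreviations cover both AEs and SAEs, is not available. This is something to confirm, not a finding.

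*A number is tempting.* Assuming that 5% to 15% of the 720 participants are readmitted for a non-fatal event gives 720 × 0.05 = 36 to 720 × 0.15 = 108. The rate is not in the article, and even if it were right the result would be an upper bound, because some of those readmissions would be life-threatening, disabling or lengthy. It does not measure the gap.

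**Conclusion.** The point holds in a limited form. The hospital criterion does not make a new admission serious in itself. A readmission that is not fatal, life-threatening, disabling or lengthy would therefore be handled as an adverse event only, outside the stated 24-hour notice and DSMB route. SAEs after discharge would be under-counted relative to a definition that counts admissions.

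The size cannot be given from the article. The conclusion rests on two premises: that the definition is applied as written, and that some participants are discharged well before 3 months, which the text allows for. It does not depend on any assumed rate.

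Nothing here touches the primary outcome, the sample size or the main analysis. Nor does the article show that classification will differ between the groups; it only leaves room for it. The change is worth making because it concerns safety oversight in an open-label trial of an intravenous product, and because it is cheap.

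**What to change.** 1. Under Safety reporting, replace the hospital clause with: *requires new hospital admission or prolongation of an existing hospital stay*. This closes the gap and removes the two readings.
2. Check the amended definition against the Interventions section, where the occurrence of an SAE is a reason for stopping treatment. A wider definition changes what that text refers to, so the two passages must be reconciled by those responsible for them.
3. Confirm that the 30-day and 3-month telephone forms capture hospital admissions. If they do not, add the question after the mRS, so that an account of an admission cannot colour the blinded rating of the primary outcome.
4. Recruitment has begun (Trial status), so apply the amended definition to adverse events already recorded. The SAE count then rests on one rule throughout.

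The cost is one clause, at most one line on an existing form, a review of events already recorded, and more SAE reports for the sites, the principal investigator and the DSMB to process.

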### Data collection

An overall schedule of trial-related activities and data collection of this study is shown in Table 1. All data will be collected on standardized CRFs designed for this study.

